### 2.8 Statistical analysis

The statistical analysis of this study covers clinical indicators, muscle and brain activation. Statistical analysis will be conducted on clinical indicators and muscle activation using SPSS 21.0 Software (IBM Corporation, New York, United States). Continuous variables with normal distribution will be presented as mean ± standard deviation, while non-normally distributed variables will be shown as median and quartiles. Categorical variables will be reported as frequency. The normality test will be performed using Shapiro-Wilk test. An independent *t*-test is applied when demographic data follow a normal distribution. Otherwise, the Mann–Whitney’s U test will be applied. The Chi-square test will be used to compare sex. Muscle activation in different groups (KOA and HC) and tasks (level walking, ascending stairs, and descending stairs) will be analyzed using mixed ANOVA or non-parametric tests (for non-normality). For brain activation analyses, a flexible factorial design (FFD) in SPM will be employed to construct a mixed-effects model including groups (inter-subject factors) and tasks (intra-subject factors) to evaluate group main effects, task main effects and their interactions. SPM will be thresholded with cluster-level false discovery rate (FDR) correction (*p* < 0.05). To explore the correlation between brain activation (HbO concentration and β value) and clinical indicators (VAS and WOMAC) in KOA patients, a multiple linear regression analysis will be performed to calculate the Pearson correlation coefficient and RMS value. Additionally, a non-linear regression prediction based on the random forest algorithm will be used to assess the importance of regression between various brain regions, muscle characteristics, and clinical indicators. All statistical tests will use a significance level of 0.05, with corrections for multiple comparisons made using the Bonferroni adjustment.

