### 2.2 Sample size calculation

The sample size for this study was determined through a priori power analysis performed using G*Power software (version 3.1.9.7) (Faul et al., 2007). Based on previous research, the study employed an Analysis of Variance (ANOVA) with repeated measures in the calculations. We expected an effect size of 0.40, an alpha error of 0.05 and a power level (1–β) of 0.20. The analysis indicated that at least 36 participants would be necessary to achieve an adequate cohort size for the study. Taking into account the participant dropouts rate 10%, the final sample size for this study was set at 40 individuals, with 20 participants allocated to each group. This sample size is considered adequate to generate reliable and valid outcomes for the research.

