### 2.4 Procedure

Before the experiment, the demographic data of all subjects will be first collected. We then explained the experimental process, test actions, and precautions to the participants. Adequate time will be provided for them to acclimate to the experimental process, ensuring a comprehensive understanding of the experimental requirements. Subsequently, fNIRS equipment and sEMG sensors will be affixed to each participant.

The experimental protocol consists of three distinct motor tasks: level walking, ascending stairs, and descending stairs. Participants will perform three tasks in a random order, with each task being repeated three times. There will be a 5 min interval between tests to allow participants to rest adequately and ensure that the fNIRS spectral signals of each test return to the baseline. Tests will be conducted on the KOA patients first, followed by the healthy controls. During the level walking, the patients will be instructed to walk at a normal, comfortable self-selected speed (SSS) for 30 s each time, with SSS defined as the average velocity from three timed baseline walks. The stair program evaluation will use standardized stairs under the same SSS conditions, maintaining consistent handrail non-use protocol across groups. The staircase consisted of 10 steps, with each step having a height of 12 cm, conforming to the standard specification for steps in China. To mitigate speed-related confounding effects, healthy controls will be pace-matched to the patient cohort’s average speed under the same conditions. A schematic overview of the experimental protocol is depicted in Figure 2. During the test, if the participant experiences any discomfort (e.g., dizziness, or falls), the testing will be immediately stopped and undergo medical evaluation of whether to continue.

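### As conventionally run, the mixed ANOVA named for sEMG drops everyone who lacks one of the three tasks, and their completed-task data with them; a linear mixed model would keep those data

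*Protocol article*

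**What the plan says.** All references are to the protocol article.

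- **Tasks (2.4 Procedure).** Level walking, stair ascent and stair descent: "Participants will perform three tasks in a random order, with each task being repeated three times". The stairs are climbed without a handrail in both groups ("maintaining consistent handrail non-use protocol across groups").
- **Stopping (2.4).** The trigger is broad: "if the participant experiences any discomfort (e.g., dizziness, or falls"). The consequence is that "the testing will be immediately stopped and undergo medical evaluation of whether to continue". The rule covers patients and controls alike.
- **Muscle analysis (2.8 Statistical analysis).** "Statistical analysis will be conducted on clinical indicators and muscle activation using SPSS 21.0 Software". Muscle activation by group (KOA, healthy control) and task "will be analyzed using mixed ANOVA or non-parametric tests (for non-normality"). The non-parametric tests are not named.
- **Brain analysis (2.8).** An SPM flexible factorial design is used to "construct a mixed-effects model including groups (inter-subject factors) and tasks (intra-subject factors").
- **Allowance for loss (2.2 Sample size calculation).** "Taking into account the participant dropouts rate 10" per cent, which takes 36 participants to 40, or 20 per group. It is a general allowance, not tied to a task or to the stopping rule.

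**The concern.** The stopping rule and the sEMG method fit together poorly. The rule makes it foreseeable that some participants will have usable data for one or two tasks but not all three. A conventional group-by-task repeated-measures ANOVA arranges the data as one row per participant with three task columns, and removes the whole row if any column is empty. Someone who completed level walking and then stopped for good on the stairs would contribute nothing, not even to the comparison of groups in level walking.

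Lost numbers are the smaller part of the problem. The larger part is who is lost. Section 2.3 requires chronic pain above 30 out of 100 in patients and no history of joint disease in controls, and the introduction says that movement under load may provoke more pain. It is therefore plausible that permanent stops on the stairs occur more in patients than in controls, and more in severe than in mild patients. In that case the KOA means for all three tasks would come from a selected subset, and a larger sample would not cure it.

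**Working it through.** **1. Reproducing the planned sample size.** Inputs from 2.2: effect size 0.40 (read as Cohen's f), alpha 0.05, repeated-measures ANOVA. Three measurements (m = 3) and a between-task correlation ρ = 0.5 are assumed, as 2.2 gives neither. For the between-group effect,

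λ = f² · N · m / [1 + (m − 1)ρ].

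With N = 36, λ = 0.16 × 36 × 3 / 2 = 8.64, and power is 0.815. With N = 34 it is 0.791. So N = 36 is reproduced at a target power of 0.80, and 36 / 0.90 = 40. (Section 2.2 prints the power as 0.20, which would give N = 8; that is a separate point.) With two equal groups, f = 0.40 means a difference of d = 2f = 0.8 SD.

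**2. Power if k KOA patients are dropped and all 20 controls stay.** λ = d² · [n₁n₂/(n₁ + n₂)] · m / [1 + (m − 1)ρ], with n₁ = 20 − k and n₂ = 20.

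| k | λ | Power |
|---|---|---|
| 0 | 0.64 × 10.00 × 1.5 = 9.60 | 0.855 |
| 2 | 0.64 × 9.47 × 1.5 = 9.09 | 0.835 |
| 4 | 0.64 × 8.89 × 1.5 = 8.53 | 0.810 |
| 5 | 0.64 × 8.57 × 1.5 = 8.23 | 0.795 |
| 6 | 0.64 × 8.24 × 1.5 = 7.91 | 0.778 |

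**3. Shift in the KOA level-walking mean if stoppers are dropped.** The article gives no stopping rate and no relation between severity and sEMG, so both are assumed. In each case every stopper has level-walking data but lacks a stair task. Let r be the correlation of severity with sEMG.

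*Sharp selection: the most severe share q all stop.* The size of the shift is r · φ(c)/(1 − q), with c the upper-q normal quantile.
- q = 0.10: φ(1.282)/0.90 = 0.195, giving 0.06 SD (r = 0.3) to 0.10 SD (r = 0.5).
- q = 0.30: φ(0.524)/0.70 = 0.497, giving 0.15 SD (r = 0.3) to 0.25 SD (r = 0.5).

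*Gradual selection: the log-odds of stopping rise by 1 per SD of severity (simulation).*

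| Share stopping | Shift, r = 0.3 | Shift, r = 0.5 |
|---|---|---|
| 13% | 0.03 SD | 0.06 SD |
| 24% | 0.06 SD | 0.10 SD |
| 33% | 0.08 SD | 0.14 SD |

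Over both models the range is about 0.03 to 0.25 SD. Against 0.8 SD that is 0.03/0.8 = 4% to 0.25/0.8 = 31%.

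**4. The same patients under a linear mixed model.** When all completed tasks are kept, the simulated level-walking mean is unbiased (0.00 SD). The stair means improve but are not fully corrected, because severity acts on stopping beyond what the observed tasks reveal. With ρ = 0.5, a stopper observed only in level walking leaves a stair bias of (1 − ρ) = one half of the complete-case bias. If just one stair task is missing, its bias is (1 − ρ)/(1 + ρ) = one third. At r = 0.5 and 24% stopping, 0.10 SD becomes about 0.05 or 0.03 SD.

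**The case against.** The strongest reply is that the article nowhere says complete-case. It names a conventional method for a 2 × 3 design, and handling of incomplete tasks is commonly left to an analysis plan, which is not shown. That is right as far as it goes: the absence of a missing-data rule is not a fault here. But 2.8 does fix the method. An analysis plan that follows it and runs the ANOVA in the usual way inherits the deletion.

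Further points stand and limit the finding:

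- **A stop need not empty a task.** Testing may resume after medical evaluation, and each task has three repeats.
- **Random order.** If the three tasks run as blocks, level walking comes first in 2 of the 6 possible orders. A patient who stops for good on the first stair task before any level walking has no level-walking data for the ANOVA to discard.
- **Severity-driven stopping is not shown.** The examples given are dizziness and falls, the rule covers controls, the tasks are short with 5-minute rests, and patients are Kellgren-Lawrence grade II or III. The examples are only examples, so knee pain would count as discomfort, but no rate is documented.
- **The size is modest.** A single-task difference between 20 and 20 has a standard error of √(2/20) = 0.32 SD, above the whole assumed range of shifts.

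A reader might also infer three stronger things that the article does not support:

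- *That the KOA group is in fact reduced to its milder members.* This needs a stopping rate and a severity relation that the article does not give.
- *That the bias must be toward no difference.* This needs greater severity to move sEMG further from control values, and the article states no direction.
- *That the correlation with VAS and WOMAC is narrowed.* Section 2.8 relates brain activation to those scores in a separate regression. Deletion inside the sEMG ANOVA removes nobody from it. Nor does the text show that the brain and muscle analyses, or the random forest, will rest on different participants.

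**Conclusion.** The point holds in a limited, conditional form. The stopping rule makes incomplete sessions foreseeable, and the sEMG method named in 2.8, as conventionally run, would discard valid data from completed tasks. If permanent stopping on the stairs is related to KOA severity, the patients retained may be milder, and the KOA level-walking mean could shift by about 0.03 to 0.25 SD, or 4% to 31% of the planned 0.8 SD. That range rests on assumed stopping in roughly 10% to 33% of patients, an assumed severity-sEMG correlation of 0.3 to 0.5, and every stopper having level-walking data but lacking a stair task. If stops are rare, resolved by resumption, or unrelated to severity, the shift is negligible. Loss of power is minor either way. This is a worthwhile, low-cost improvement to a stated method, not a flaw that undermines the study.

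**What to change.** In 2.8, replace the mixed ANOVA for muscle activation with a linear mixed model: fixed effects for group, task and group × task, a random participant intercept, REML estimation, and every completed task included whether or not the participant completed the others. Tabulate stops by group and task beside the group contrasts, so that a reader can judge whether selection is a practical issue. To support that table, record the task, the repetition and the reason at each stop.

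The cost is a sentence of analysis text, one field on the test record and slightly more modelling work. SPSS already offers the procedure. The model relies on a missing-at-random assumption, which is weaker than what dropping incomplete participants requires but, as shown above, does not remove all bias from the stair means. The sample size, the tasks and the stopping rule are unaffected.

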**FIGURE 3 F3:**
[figure not shown]
**(A)** Near-infrared spectroscopy-statistical parametric mapping toolbox (NIRS-SPM) channel configuration and numbering. **(B)** Schematic representation of fNIRS channel. fNIRS, functional near-infrared spectroscopy.

This study will use the near-infrared spectroscopy-statistical parametric mapping toolbox (NIRS-SPM) implemented in MATLAB to process raw light intensity data obtained from Oxysoft software. The hmrIntensity2OD function is used to convert the data to optical density after eliminating low-quality channels. Head motion artifacts are mitigated using moving standard deviation, spline interpolation, and wavelet artifact correction methods (Guan et al., 2024). The corrected signal is filtered with a bandpass filter to remove physiological noise. The optical density data is transformed into relative changes in HbO and HbR through the modified Beer-Lambert law. Because studies have demonstrated that the HbO concentration possesses a high signal-to-noise ratio, being the most sensitive indicator of local cerebral hemodynamic responses (Gagnon et al., 2012; Ohshima et al., 2023). Moreover, over time, it exhibits higher repeatability and stability (Strangman et al., 2002; Plichta et al., 2006). Therefore, HbO will be chosen as the follow-up analysis in this study. After data preprocessing, we will use the general linear model (GLM) in spectroscopy-statistical parametric mapping (SPM) to model the changes in the concentration of HbO, obtaining the regression coefficient β value for each task condition (Wei et al., 2024). The β value reflects the amplitude of the task-induced blood oxygen signal change and can be used as a quantitative indicator of the neural activation intensity in the corresponding channel region. The design matrix in the model incorporated block-based conditions (boxcar function) corresponding to the three motor tasks, which are convolved with the hemodynamic response function (HRF) to account for the temporal delay inherent in neural activity. Group-level analysis extracts the HbO concentration changes and β values in predefined brain ROIs for subsequent statistics.

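### The group main effect in brain activation is assigned to a single-error flexible factorial model that does not by itself supply the between-subject error this effect needs

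*Protocol article*

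**What the plan says.** Section 2.8 of the protocol article gives the brain data one model: "a flexible factorial design (FFD) in SPM will be employed to construct a mixed-effects model including groups (inter-subject factors) and tasks (intra-subject factors"). The model is meant "to evaluate group main effects, task main effects and their interactions". The text names group and task as factors. It names no subject factor, no error term for the group effect and no covariance (non-sphericity) setting.

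On error control, the same section says "SPM will be thresholded with cluster-level false discovery rate (FDR) correction" at p < 0.05, and "All statistical tests will use a significance level of 0.05" with Bonferroni adjustment for multiple comparisons. For muscle activation, with the same two factors, it plans a mixed ANOVA, or non-parametric tests if the data are not normal.

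Section 2.5 states: "Group-level analysis extracts the HbO concentration changes and β values in predefined brain ROIs for subsequent statistics". The β values per region of interest (ROI) will therefore be available outside the SPM model.

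Section 2.2 bases the sample size on a repeated-measures ANOVA: "the study employed an Analysis of Variance (ANOVA) with repeated measures in the calculations". It states "We expected an effect size of 0.40, an alpha error of 0.05 and a power level (1–β) of 0.20" and concludes that "at least 36 participants would be necessary", raised to 40 (20 per group) for 10% dropout. It gives no correlation among the repeated measures and does not say whether the between-group, within-subject or interaction test was powered.

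**The concern.** Each participant contributes three task values. Two sources of variation follow: differences between participants within a group, and task-to-task variation within a participant. The task effect and the group-by-task interaction are properly judged against the second. The group main effect must be judged against the first, which is the larger whenever a participant's three values are positively correlated.

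A flexible factorial model carries a single residual variance. With a subject factor in the model, that residual is the within-subject one, which is too small a yardstick for comparing KOA patients with controls. The plan nevertheless asks this one model for all three effects.

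Section 2.1 describes the study as a comparison of activation patterns between patients and controls, and the Discussion wants to nominate cortical regions as intervention targets. Group differences that are too easily declared would feed directly into that.

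**Working it through.** **Inputs.** From the article: 2 groups, 3 tasks (m = 3), 20 per group (N = 40; 36 before dropout), α = 0.05, effect size 0.40 (read as Cohen's f). The correlation ρ between a participant's task values is not stated, so it is an assumption, shown over 0.2 to 0.7. Equal correlation between all pairs of tasks is also assumed.

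**Step 1: the plan's own figure.** For the between-group test in a repeated-measures ANOVA, λ = f²·N·m / (1 + (m − 1)ρ), with df 1 and N − 2.
- At N = 36 and ρ = 0.5: λ = 0.16 × 36 × 3 / 2 = 8.64, and power is 0.815. At N = 34: λ = 8.16, and power is 0.791.
- So 36 is the smallest even N with power of at least 0.80, and 36 / (1 − 0.10) = 40. Both stated figures reproduce.
- On the same search, ρ = 0.45 gives 34 and ρ = 0.55 gives 38. The interaction test at ρ = 0.5 would need only 12.
- The printed power of 0.20 is read as β = 0.20. A power of 0.20 would need only about 8 participants.

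Hence ρ = 0.5 is the value that reproduces N = 36 if the between-group test was powered at 0.80.

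**Step 2: size of the mismatch.** With total variance 1 and no group effect, the group mean square has expectation 1 + 2ρ and the within-subject mean square has expectation 1 − ρ. The F ratio is therefore inflated by (1 + 2ρ)/(1 − ρ), which at ρ = 0.5 is 2.0/0.5 = 4.

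**Step 3: false-positive rate on the within-subject residual.** Rate = P[F(1, 2(N − 2)) > F₀.₀₅ / inflation]. At N = 40 the df are 1 and 76, F₀.₀₅ = 3.967, and at ρ = 0.5 the threshold is effectively 3.967/4 = 0.992.

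| ρ | Inflation | Rate, N = 36 | Rate, N = 40 |
|---|---|---|---|
| 0.2 | 1.75 | 13.6% | 13.6% |
| 0.3 | 2.29 | 19.1% | 19.2% |
| 0.5 | 4.00 | 32.2% | 32.3% |
| 0.7 | 8.00 | 48.3% | 48.4% |

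Simulation (60,000 runs per setting) agrees: 0.322 at ρ = 0.5 for both sample sizes.

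**Step 4: other set-ups, simulated at ρ = 0.5.**
- No subject factor, rows treated as independent: inflation is about 1 + 2ρ = 2, and the rate is 16.5% (N = 36) or 16.3% (N = 40).
- Repeated-measures covariance estimated and used for the group contrast, pooled df kept: 5.6% or 5.5%.
- Group tested against participants within groups, df 1 and N − 2: 5.0%.

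**Step 5: does the multiplicity correction help?** With Bonferroni over six ROIs the nominal level is 0.05/6 = 0.83%. At N = 40 and ρ = 0.5 the critical F is 7.339. Dividing by 4 gives 1.835, and the rate per ROI is about 18%. The correction does not restore the level.

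**The case against.** The strongest objection is that the article does not say the within-subject residual will be used. It lists only group and task and calls the model mixed-effects. That wording could describe a set-up without a subject factor in which the repeated-measures covariance is estimated, and the group test is then close to nominal. Subject factor, error term and covariance option are also details that a condensed article may leave to a full analysis plan. This stands as far as it goes. A reader might infer that the group effect will be tested at a 32% error rate, or that no flexible factorial set-up can ever give a usable group test; the documents support neither. What remains is a stated choice: one single-error model is assigned an effect whose error it does not by itself provide, and two of the three set-ups examined give a group test that is clearly too liberal.

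Second, ρ = 0.5 is back-calculated, and only if the between-group test was the one powered, at 0.80. It is a planning value, not an estimate for the HbO β values. This also stands, which is why a range is given.

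Third, a reader might take 32% to mean that about one null region in three would be reported as different. That does not follow: it is the rate of a single uncorrected test, and the maps are thresholded with cluster-level FDR, whose resulting error rate was not computed. The correction still works on the p-values it receives, and Step 5 shows that Bonferroni does not repair them.

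Fourth, the scope is limited. Task and interaction tests are sound on the within-subject residual, and the mixed ANOVA for muscle activation separates the two errors. The Introduction also names correlation with pain and function scores as the specific objective, so it is arguable whether group is the main comparison.

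**Conclusion.** The concern holds in conditional form. Section 2.8 assigns the group main effect in brain activation to a model with one residual variance and does not fix the error term that this effect needs. The size depends on the set-up: about 14% to 48% at a nominal 5% if a subject factor is fitted and its residual is used (ρ from 0.2 to 0.7), about 16.5% at ρ = 0.5 if rows are treated as independent, and about 5.5% if the repeated-measures covariance is estimated and used for the group contrast. The figures assume equal correlation between tasks and normal errors. The article does not establish which set-up is intended, so no single rate can be attributed to the plan.

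**What to change.** Test the group main effect at participant level and say so in section 2.8. Either average each participant's three task β values per ROI (or channel) and compare groups with a two-sample model on N − 2 df, or fit a mixed ANOVA or a linear mixed model with a random participant intercept, so that group is judged against the between-subject error. The article already plans the mixed-ANOVA form for muscle activation. Keep the flexible factorial for the task and group-by-task effects, and apply the planned multiplicity correction to the resulting group p-values.

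The cost is a change of wording and a few lines of code. No new data are needed, because the ROI β values are already to be extracted. The downside is that group p-values will be larger than those from a test on the within-subject residual.

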**Discussion:**

This study, based on “differential activation of the sensory-motor cortex under movement,” innovatively observes the relationship between pain and functional impairment in KOA patients and activation levels in specific brain regions across different motor environments. This not only provides a basis for early prediction of KOA onset but also offers potential targets for clinical interventions in KOA. Ultimately, the results of this study may open new perspectives for the rehabilitation of chronic musculoskeletal diseases.

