This study adopts a cross-sectional research design and utilized fNIRS to investigate brain activities changes in KOA patients under different movement contexts. The specific objective is to analyze the correlation between these changes and the patients’ pain and functional scores. This will provide a more powerful theoretical basis for the central intervention programs for KOA patients.

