### 2.5 fNIRS data acquisition and preprocessing

A portable multi-channel wireless fNIRS device (Brite24, Artinis Medical Systems, Netherlands) will be employed to capture cerebral fNIRS signals to evaluate alterations in brain activity patterns during movement. Following the international 10–20 system for electrode placement, the Cz electrode location of participants is identified using three-dimensional digitizer (Patriot, Polhemus): the intersection of the sagittal plane (connecting the nasion and inion) and the coronal plane (linking bilateral preauricular points) defines the standardized positioning of the Cz electrode. This will allow channel positions to be mapped to the Montreal Neurological Institute (MNI) coordinate system, enabling precise spatial normalization across participants. Subsequently, we will measure the head circumference of each participant to select a suitable size head cap equipped with a fNIRS probe. The elastic cap with adjustable sliding mounts allowed dynamic adaptation of source-detector spacing (25–35 mm) based on real-time scalp coupling verification via optical intensity monitoring. This hybrid spatial referencing strategy adapts to changes in scalp curvature and hair density, ensuring optimal light penetration and signal-to-noise ratio.

This system enabled the measurement of oxygenated hemoglobin (HbO) and deoxygenated hemoglobin (HbR) (Ferrari and Quaresima, 2012). The system emits near-infrared light at 670 nm and 850 nm wavelengths with a 10 Hz sampling frequency. Each sensor within the apparatus comprises a light-emitting diode paired with a detector photodiode. In total, the configuration includes 10 light sources and eight detectors, resulting in the formation of 24 channels. As shown in Figure 3. The three-dimensional digital recording of fNIRS channel positions mainly covers six specific brain regions of interest (ROIs) in both hemispheres: primary somatosensory cortex (S1), primary motor cortex (M1), and somatosensory association cortex (SAC). These ROIs focused in this study play an important role in sensory processing and motor execution in the central nervous system (Anders et al., 2004; Bhattacharjee et al., 2020; Sansare et al., 2024). In addition, our previous studies have found that these regions are associated with changes in KOA (Yang et al., 2024).

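### The brain–symptom objective rests on a multiple regression that does not give the Pearson correlation it names, and in 18–20 patients noise alone inflates the size of its R

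*Protocol article*

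**What the plan says.** The Introduction sets the aim: "The specific objective is to analyze the correlation between these changes and the patients’ pain and functional scores". Section 2.8 analyses this in the KOA patients only. HbO concentration and β are the brain measures, and VAS and WOMAC are the clinical scores. The method is given as "a multiple linear regression analysis will be performed to calculate the Pearson correlation coefficient and RMS value". A second analysis follows: "a non-linear regression prediction based on the random forest algorithm will be used to assess the importance of regression", covering brain regions, muscle characteristics and clinical indicators. The section closes with a 0.05 significance level and a Bonferroni adjustment.

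The size of the data is fixed elsewhere. Section 2.2 plans 40 people, "with 20 participants allocated to each group", allowing for 10% dropout. Section 2.5 says the recording "mainly covers six specific brain regions of interest (ROIs) in both hemispheres", and that β is obtained by fitting a general linear model to the HbO signal. Section 2.4 has three walking tasks. Section 2.6 defines RMS as the root mean square of the sEMG signal.

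The Discussion part of the Abstract says of the study: "This not only provides a basis for early prediction of KOA onset". Section 3 repeats the idea in softer terms.

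**The concern.** The method does not match the quantity it is said to produce. A regression on several regions returns coefficients and a multiple R, the correlation between fitted and observed scores. It does not return a Pearson correlation between a region and a score. The RMS in the same sentence could be the error of the fit or the sEMG index, because the article uses that abbreviation only for the latter.

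The distinction matters because multiple R can only rise as terms are added, whether or not they carry information. With 18 to 20 patients the rise is large. A random forest likewise always places some variable first. Section 3 intends to draw potential intervention targets from this analysis, so a large R and a ranked list of regions could be read as evidence when there is none. The claim about onset goes further than any cross-sectional result can.

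**Working it through.** **Inputs.** KOA patients: 20 (Section 2.2), or 20 × 0.9 = 18 after dropout. Regions: 6 (Section 2.5). Tasks: 3 (Section 2.4). Brain measures: 2, and clinical scores: 2 (Section 2.8). The number of regression terms is not stated, so the values of p below are assumptions.

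**The plan's own figure first.** Section 2.2 gives 36 participants from a repeated-measures ANOVA with f = 0.40 and α = 0.05. Taking the between-group effect, 3 measurements and an assumed correlation of 0.5, the noncentrality is f²·N·m / (1 + (m − 1)ρ) = 0.16 × 36 × 3 / 2 = 8.64. Power at N = 36 is then 0.815, and 36 is the smallest even N reaching 80%. Then 36 / 0.9 = 40. The figure reproduces if the stated power level of 0.20 is read as 0.80. It sizes the ANOVA, not the correlation objective.

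**Multiple R under no association.** With p terms and n patients, R² follows a Beta(p/2, (n − p − 1)/2) distribution, with mean p/(n − 1). For p = 6 and n = 20 the mean is 6/19 = 0.32; for p = 12 it is 12/19 = 0.63.

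| Terms p | Median R, n = 20 | Median R, n = 18 | P(R > 0.5), n = 20 | R needed for F test at 5%, n = 20 |
|---|---|---|---|---|
| 1 | 0.16 | 0.17 | 2% | 0.44 |
| 3 | 0.37 | 0.39 | 19% | 0.61 |
| 6 (one per region) | 0.55 | 0.58 | 64% | 0.76 |
| 12 (HbO and β per region) | 0.80 | 0.85 | 99% | 0.93 |

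Correlation among the regions does not change these values as long as the model has full rank.

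**The same noise judged out of sample.** In 4,000 simulated data sets with independent normal predictors and n = 20, the median leave-one-out r was −0.17 (3 terms), −0.09 (6) and 0.00 (12). The apparent association disappears.

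**Random forest.** Importance is a relative ordering. Some region is always first, including when every region is noise. A Bonferroni adjustment acts on p-values, so it corrects neither this ordering nor the size of R.

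**If the Pearson coefficients are bivariate instead.** One brain measure gives 6 × 3 × 2 = 36 correlations and two measures give 72. At n = 20, treating the tests as independent, the largest null |r| has a median of 0.52 to 0.56. The Bonferroni threshold is |r| of 0.67 to 0.69. False positives are controlled, but power for a true r of 0.5 is only 15% down to 10%.

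**Onset.** Section 2.3 enrols patients with established KOA (Kellgren-Lawrence II or III, pain for at least 3 months) and healthy controls. Section 2.1 makes the study cross-sectional. No one is followed to onset.

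**The case against.** Several stronger conclusions are tempting, and the document does not support them.

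- A reader might infer that fit will be judged on the same patients used for fitting. Section 2.8 names no validation scheme, but it does not say this either. A condensed article can leave such detail to the full protocol or analysis plan.
- A reader might infer more predictors than patients, by multiplying regions by tasks and adding 14 sEMG indices (7 muscles × 2). The count of terms is not given. The sentence on regression covers brain activation only, and muscle features appear only in the forest sentence. With one to three terms the inflation is modest.
- A reader might infer that noise will be declared significant. It will not be, beyond the nominal rate. With six terms and n = 20 the F test needs R of about 0.76, so a typical noise value of 0.55 fails it.
- A reader might fault the forest for a high fitted correlation. The plan asks it for importance, not for a correlation.

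It can also be said that Pearson may mean simple bivariate coefficients, that the wording is exploratory, and that Sections 2.1 and 2.2 put the group comparison first. These points are fair, and they limit the criticism to the named statistic, the size of R and the ranking. They do not remove it. The sentence still assigns a Pearson coefficient to a multiple regression, the Introduction still calls this the specific objective, and the onset claim stands apart from any model choice. Section 3 does hedge its version of that claim and disclaims causality, but the Abstract's version is unqualified.

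**Conclusion.** The point holds in a limited form. The statistic named for the specific objective does not come from the method named, and one of the two reported quantities is ambiguous. In 18 to 20 patients with no true association, the multiple R has a median of about 0.55 to 0.58 with one term per region and 0.80 to 0.85 if HbO and β both enter for each region. With one to three terms it is 0.16 to 0.39. These figures depend on an assumed number of terms, and they apply to R as fitted. The type I error of the overall test is not affected. What is inflated is the reported size, and what is unprotected is the importance ranking; the stated Bonferroni rule reaches neither. The Abstract's onset claim is unsupported by the design.

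**What to change.** In Section 2.8:

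1. Use β alone as the activation measure, since it is fitted from the same HbO signal.
2. For regions named in advance, report simple or partial Pearson or Spearman correlations of β with VAS and with WOMAC, each with a 95% confidence interval, under the Bonferroni adjustment already stated. Naming few regions helps: with 12 tests rather than 36, power for a true r of 0.5 at n = 20 is 25% rather than 15%.
3. Report any multivariable or forest result only as leave-one-out or out-of-bag r and RMSE, and importance only against a permutation null. Label both exploratory.
4. Call the prediction error RMSE, leaving RMS for the sEMG index.

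In the Abstract, delete the claim about early prediction of onset, and remove its echo in Section 3.

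The cost is some rewording, a few lines of code and smaller reported associations, with no additional patients. The intervals will be wide: for r = 0.5 and n = 20, Fisher's z gives 0.549 ± 1.96/√17 = 0.549 ± 0.475, that is about 0.07 to 0.77.
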